### [name] Lab

The laboratory facilities of [name] are housed on the second floor of the MIND Institute Wet laboratory building on the UC Davis Medical Center Campus in Sacramento, CA. The [name] laboratory consists of 600 sq feet of wet laboratory space dedicated to immunological analysis and contains instrumentation and facilities for this function. Further resources include an additional 200 sq feet space dedicated to the housing of a BD Biosciences LSRII flow cytometer and

[figure not shown]

A pilot study examining the microbiotal composition in children with autism after use of *Bifidobacterium infantis* and milk oligosaccharides.

associated computational instrumentation, plus a Luminex workstation and instrumentation for multiplexing technology. Within the research wet laboratory building all important facilities are present including computer and internet hookups, tissue culture room, dark room, and common equipment rooms. The research wet laboratory building is adjacent to the MIND clinical facility. [name] laboratory has all the major equipment required for immune-based studies, including a BD LSRII flow cytometer equipped with a solid-state Coherent Sapphire100mW 488nm laser (blue), a Coherent radius 25mW 640nm HeNe laser (red), and a solid-state 50mW 405nm laser (violet) and 11 PMTS for enhanced fluorochrome color detection. The LSRII flow cytometer instrumentation is supported by a dedicated PC workstation, software and printer. Further instrumentation includes: Luminex100 with a dedicated PC workstation and software, Victor3V ELISA plate reader with a dedicated PC workstation and software, Baker Bioguard laminar flow hoods, high speed centrifuges, pH meters, analytical balances, Zeiss fluorescent microscope, two Hereaus CO2 incubators, refrigerators, -20° and -80°C freezers. Additional office space is dedicated for data analysis and data management. Additional support core facilities that house additional refrigerators, freezers, photographic development facilities, autoclaves and facilities for washing glassware are available within the Wet laboratory facility at the MIND Institute.

Offices: The MIND. Institute has office space available for the Center's administrative assistant. All office space includes up-to-date computers, high-speed internet access, printers and telephones with private voice mail.

**Evolve Biosystems** manufactures proprietary and targeted blends of synbiotic products that contain metabolically active probiotics with matched human equivalent prebiotics based on research from the University of California Davis Foods for Health Institute.

Evolve Biosystems is using a contract manufacturer to produce the *B.infantis* for this study. The contract manufacturer is Culture Systems, Inc, founded in 1991. Culture Systems Inc. focuses on research and development, marketing, and manufacturing of dairy and probiotic cultures. Culture products from their plant have been used in the food industry since its inception. They produce all products under GMP practices, receive inspections from the health department and FDA, and issue a Certificate of Analysis for each batch including pathogen control as part of our QC process. Their facilities include 4 industrial fermentation/harvesting systems and several freeze-driers in 18,000 SQ of space. They currently manufacture cultures for several dairy companies and animal feed companies. They are capable of producing various lactic cultures.

**Sterling Technologies** has GMP, dairy and food grade production facilities in South Dakota that has a capacity to process 105,000 gallons of colostrum per week. The colostrum product is a commercial product produced under GMP conditions. The whole colostrum is defatted and the casein removed to produce the product being used here. Separation of casein and whey fractions is standard practice in the dairy industry. Certificate of analysis is provided for each batch of product. Stimulac has been sold into the human nutrition market as a dietary supplement for 25 years. The bovine colostrum product has been sold as an dietary supplement into the autistic community for the past 15 years in aiding the immune system and enteric system of children with autism sold under the trade name ColostrumGold. This is a liquid product bottled in 4 oz containers that must be refrigerated after opening. Sterling has agreed to freeze dry the prebiotic product for this study.

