## 4 Objectives

**AIM 1. To characterize stool microbiotal composition and immune markers after administration of a probiotic with and without a prebiotic in children with autism.**

Hypothesis 1.1: Synbiotic administration of *Bifidobacterium infantis* (probiotic) and bovine milk oligosaccharides (prebiotic) will alter the composition of stool microbiota, with greater increases in commensal actinobacteria (including *B. infantis*) and decreases in pathogenic proteobacteria than *B. infantis* alone.

Hypothesis 1.2: Synbiotic administration of *Bifidobacterium infantis* and bovine milk oligosaccharides will alter serum immune (cytokine, immunoglobulin) measures.

**AIM 2 (exploratory). To determine tolerability of *Bifidobacterium infantis* and bovine milk oligosaccharides in children with autism.**

Hypothesis 2.1: *Bifidobacterium infantis* and bovine milk oligosaccharides will be well tolerated in children with autism, as measured by gastrointestinal and behavioral symptoms.

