## 11 Procedures Involved

This pilot study is a randomized, controlled trial of a synbiotic (BMO + *B. infantis*) vs. BMO alone.

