### Synbiotic/BMO only administration

Each participant will be randomized by the IDS pharmacy to receive either the synbiotic first or the BMO first in a cross-over study design. This is a double blind study in that both participants and study personnel will not be aware of which treatment arm the participant will receive first. The study supplement will be dispensed in identically packaged pouches. The study will last 12 weeks, including 5 weeks of BMO use, 5 weeks of the synbiotic, and a two-week washout period in between.

A pilot study examining the microbial composition in children with autism after use of *Bifidobacterium infantis* and milk oligosaccharides.

The synbiotic and the BMO will be given once a day. Each synbiotic dose will be **100 mg of *B. infantis*, or 10 Billion CFU ( $1 \times 10^{10}$ )**, delivered once a day with **0.15 g/pound body weight per day of BMO**. The **BMO only arm** will be the identical dose of 0.15 g/pound body weight/day BMO given orally. The synbiotic or BMO will be a powder the parent can deliver in many different recipes including any cold milk-based liquid, ice-cream or pudding. Parents will be provided an individualized recipe booklet that provides dosing strategies and instructions as well as a magic bullet blender to facilitate supplement incorporation into food items. Parents will also be instructed to store the study drug in the freezer and to ensure the child consumes the entire supplement dose within 20 minutes.

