## 26 Local Number of Subjects

This study intends to have 10 subjects complete the study protocol, and we expect to enroll up to twenty subjects to account for screening failures and early terminations.

**Power Analysis:** The proposed two-period crossover study design with baseline and follow-up measurements for each period will enable each child to serve as their own control for purposes of quantifying the effects of synbiotic on microbiotic outcomes. The effect size parameter of interest will be the mean within-child between-period (synbiotic vs. prebiotic) difference in within-period change (from baseline to follow-up). With an analysis of ten children, the proposed study design will allow us to estimate the parameter of interest with sufficient precision that the margins of error (i.e. halfwidths of 95% confidence intervals) will be 1.4 root mean square error (rmse) wide. In addition, the study will have **80% power** to detect differences of magnitude 1.94 rmse, under two-sided testing (with  $\alpha=5\%$ ) of the null hypothesis that the effect size is 0. The rmse is the square root of the residual error variance component. The residual error variance component is equal to  $(1 - R) * V$ , where R is the within-child correlation and V is the total variance of the outcome distribution. To our knowledge, no estimates are available of the within-child correlation for the proposed outcomes in this clinical population. (Indeed, this is one of the knowledge gaps that the pilot study will aim to fill.) However, [name] lab have measured similar bifidogenic response in infants, for whom the within-infant correlations have ranged as high as 40%. Although it is plausible

[figure not shown]

A pilot study examining the microbiotal composition in children with autism after use of *Bifidobacterium infantis* and milk oligosaccharides.

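### Aim 1 and Hypothesis 1.1 set the synbiotic against B. infantis alone, but the crossover compares it with BMO alone, so Hypothesis 1.1 as written cannot be tested

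*Protocol*

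**What the plan says.** Section 4 (Objectives) frames the main aim around adding a prebiotic to a probiotic. Aim 1 concerns stool microbiota and immune markers "after administration of a probiotic with and without a prebiotic in children with autism". Hypothesis 1.1 keeps the same direction: the synbiotic should give larger rises in commensal actinobacteria and larger "decreases in pathogenic proteobacteria than *B. infantis* alone".

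The rest of the Protocol describes a different comparison. Section 5 (Background) says the pilot explores whether the synbiotic changes more than the prebiotic alone. Section 11 calls the study a "randomized, controlled trial of a synbiotic (BMO + *B. infantis*) vs. BMO alone". Its dosing subsection sets a 12-week course, "including 5 weeks of BMO use, 5 weeks of the synbiotic, and a two-week washout period in between", with BMO at 0.15 g per pound of body weight per day in both periods. In section 26 the parameter for power is the "mean within-child between-period (synbiotic vs. prebiotic) difference in within-period change (from baseline to follow-up").

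On the prebiotic itself, which is common to both periods, the manufacturer text states: "The whole colostrum is defatted and the casein removed to produce the product being used here".

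**The concern.** The aim varies the prebiotic and holds the probiotic fixed. The design varies the probiotic and holds the prebiotic fixed. These are different scientific questions. Hypothesis 1.1 is also the directional hypothesis for the primary endpoint, change in intestinal microbiota (section 10).

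What is at stake is the reading of the result. If the crossover favours the synbiotic, the finding is that B. infantis adds something when given with BMO. Under the present wording it could be reported as support for Hypothesis 1.1, that is, that BMO adds something to B. infantis. An analysis plan cannot repair this, because it cannot analyse a condition that no child receives.

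**Working it through.** **1. The two comparisons side by side.**
- Section 4, Aim 1 and Hypothesis 1.1: (B. infantis + BMO) against B. infantis alone. The component that varies is BMO.
- Sections 5, 11 and 26: (B. infantis + BMO) against BMO alone. The component that varies is B. infantis.

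Aim 1 and Hypothesis 1.1 agree with each other, and the other three sections agree with each other. The reversal is therefore confined to section 4, but it is not one misplaced word.

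**2. Exposure by week (section 11).**
- BMO alone 5 + washout 2 + synbiotic 5 = 12 weeks.
- On BMO: 5 + 5 = 10 weeks.
- On B. infantis: 5 weeks, all with BMO.
- On B. infantis without BMO: 5 − 5 = 0 weeks.

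**3. What each contrast measures.** Let P be the effect of BMO as given, B the effect of B. infantis on its own, I their interaction, and T1 and T2 the time effects in periods 1 and 2. Assume no carryover past the washout. I is kept in the model because section 5 says oligosaccharides stimulate the activity of B. infantis. The mean within-period changes are:
- Synbiotic first: P + B + I + T1, then P + T2.
- BMO first: P + T1, then P + B + I + T2.

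Averaged over the two sequences, synbiotic minus BMO is (P + B + I) − P = B + I, since the time effects cancel. This is the effect of B. infantis given with BMO.

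Hypothesis 1.1 needs (P + B + I) − B = P + I, the effect of BMO given with B. infantis. No combination of the four means gives P + I, because I never appears without B. Setting T1 = T2 = 0 does not help: it yields P and B + I separately, still not P + I. An indirect answer would need both no time effects and I = 0, and the second runs against the premise of the study.

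**4. The power figures belong to the contrast that is run.** Inputs from section 26: n = 10, two-sided 5%, 80% power, within-child correlation 0.40.
- A difference of two changes has variance 4 rmse², so SE = 2/√10 = 0.632 rmse.
- Half-width with 9 degrees of freedom: 2.262 × 0.632 = 1.43 rmse. The plan states 1.4.
- Detectable difference: (2.262 + 0.842) × 0.632 = 1.96 rmse, or 1.99 by the noncentral t. The plan states 1.94, which is within 3%.
- At correlation 0.40: 1.4 × √0.6 = 1.08 SD and 1.94 × √0.6 = 1.50 SD. The plan states 1.1 and 1.5.

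These figures reproduce closely for synbiotic against BMO alone. None of them applies to synbiotic against B. infantis alone.

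**The case against.** The strongest defence is that the Protocol gets the comparison right everywhere else. Section 5 puts the primary goal as stool microbiota after the synbiotic, compared with baseline, and then names the prebiotic alone as the comparator. Procedures, dosing and power follow that, and Aim 1 is a descriptive aim in a pilot hoping for ten completers. All of this is correct, and it limits the fault to the wording of section 4. It does not remove the fault, because Hypothesis 1.1 makes an explicit comparison with a condition that is never given.

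Three stronger readings are tempting, and the documents do not support them.

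- **The prebiotic is mislabelled.** A reader might infer this from the manufacturer text before section 24: "The whole colostrum is defatted and the casein removed to produce the product being used here". But section 5 discloses that the BMO comes from bovine colostrum, and section 5 refers to Appendix 1 for the product description, which is not in the text at hand. Nothing can be concluded here about oligosaccharide content or further processing.
- **Aim 2 fails with it.** Hypothesis 2.1 expects that B. infantis and "bovine milk oligosaccharides will be well tolerated in children with autism, as measured by gastrointestinal and behavioral symptoms". This concerns the tolerability of what the children are given, in an aim marked exploratory. It makes no comparison with B. infantis alone and no claim about isolated oligosaccharide.
- **The crossover isolates the effect of B. infantis as such.** That holds only without interaction. The contrast gives the effect of B. infantis in the presence of BMO.

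**Conclusion.** The point holds for Aim 1 and Hypothesis 1.1 only. Both reverse the comparator that the trial uses, and with 0 of 10 treatment weeks on B. infantis alone, the comparison in Hypothesis 1.1 has no data at any sample size. This is more than clerical, since it decides which component a positive result is credited to.

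The randomised contrast is sound for its own question, and its sample size and power basis are unaffected. The central finding needs only the treatment schedule in section 11. The statement that the contrast measures B. infantis given with BMO also assumes no carryover past the two-week washout.

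**What to change.** In section 4, restate Aim 1 as the prebiotic (BMO) with and without B. infantis. Restate Hypothesis 1.1 as greater increases in commensal actinobacteria and greater decreases in pathogenic proteobacteria with the synbiotic than with BMO alone. Add that the crossover contrast supports a conclusion only about the added effect of B. infantis when given with BMO, and that no claim will be made about what BMO adds to B. infantis.

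The cost is a wording amendment. Treatment, sample size and the power calculation do not change. The trial gives up only a claim that it could not have supported.

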## 24 Prior Approvals

The MIND Institute Pilot Grant Awards Committee approved funding for this study on November 27, 2012.

## 25 Recruitment Methods

[figure not shown]

A pilot study examining the microbiotal composition in children with autism after use of *Bifidobacterium infantis* and milk oligosaccharides.

Twenty children with autism/ASD and irregular bowel movements ages 2-11 years of age will be recruited for this study in hopes of having ten children complete the protocol. Recruitment strategies will include solicitation of families who have participated in [name] Speaks study "Defining the Underlying Biology of Gastrointestinal Dysfunction in Autism," all of whom participated in the CHARGE (Childhood Autism Risks from Genetics and the Environment) study and received autism diagnostic assessments. Additionally, only families that indicated a desire to be contacted for future studies will be solicited.

We will also contact families who have participated in prior research at the MIND Institute and who have agreed to be contacted for future studies through the MIND Research Volunteer Registry. These families will initially be contacted either by phone or email and asked to participate in an oral consent questionnaire to evaluate eligibility. A flyer explaining the study will also be made available to families in clinic. Upon completion of the questionnaire, and approval from [name], the participant and his or her family will be invited to complete a screening visit for the study.

Participants will receive a total of \$85 for participating in the study. Of this, \$50 will be in the form of gift cards, the remaining \$35 will come in the form of a magic bullet blender, with which the family is able to mix the study supplement into food or drink for consumption throughout the study. The family is able to keep after the study.

## 26 Local Number of Subjects

This study intends to have 10 subjects complete the study protocol, and we expect to enroll up to twenty subjects to account for screening failures and early terminations.

**Power Analysis:** The proposed two-period crossover study design with baseline and follow-up measurements for each period will enable each child to serve as their own control for purposes of quantifying the effects of synbiotic on microbiotic outcomes. The effect size parameter of interest will be the mean within-child between-period (synbiotic vs. prebiotic) difference in within-period change (from baseline to follow-up). With an analysis of ten children, the proposed study design will allow us to estimate the parameter of interest with sufficient precision that the margins of error (i.e. halfwidths of 95% confidence intervals) will be 1.4 root mean square error (rmse) wide. In addition, the study will have **80% power** to detect differences of magnitude 1.94 rmse, under two-sided testing (with  $\alpha=5\%$ ) of the null hypothesis that the effect size is 0. The rmse is the square root of the residual error variance component. The residual error variance component is equal to  $(1 - R) * V$ , where R is the within-child correlation and V is the total variance of the outcome distribution. To our knowledge, no estimates are available of the within-child correlation for the proposed outcomes in this clinical population. (Indeed, this is one of the knowledge gaps that the pilot study will aim to fill.) However, [name] lab have measured similar bifidogenic response in infants, for whom the within-infant correlations have ranged as high as 40%. Although it is plausible

[figure not shown]

A pilot study examining the microbiotal composition in children with autism after use of *Bifidobacterium infantis* and milk oligosaccharides.

to assume that correlations will be larger in older children, we conservatively assume a within-child correlation of 40%. Using the above expressions, we anticipate the margin of error of our parameter estimate to be 1.1 standard deviations (SD) and the minimum detectable difference to be 1.5 standard deviations, where the standard deviation is the square root of the total variance  $V$ . In case the correlation is as high as 70%, the margin of error and the minimum detectable difference will be less than 0.7 and 1.1 SD, respectively. For the range of correlations that we considered, from 0.4 to 0.7, the proposed study will yield sufficiently precise estimates to achieve the research objectives of the proposed pilot study and develop evidence that can be used to inform future research in this population.

We believe that we will be able to recruit all of our participants locally given our access to the thousands of families with autism spectrum disorders that have participated in research at the MIND Institute.

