### **Stool Collection**

Baseline stool samples will be collected within 48 hours prior to the first dose of synbiotic. Subsequent samples will be taken after completing the first study arm at week 5, after completing the washout period at week 7, and after completing the second arm of the study at week 12.

Families will be given a kit including a styrofoam container with an ice pack, and a sterile tongue blade. Stool samples will be collected at home by the parent prior to their study visit into a sterile specimen container using a sterile tongue blade and kept cold in either a styrofoam transport container with ice pack or their home freezer until the visit.

Stool samples will be analyzed for microbial composition, microbial metabolites, peptide profile, intestinal permeability (zonulin), and pancreatic insufficiency (elastase-1).

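### Subtracting each period's baseline doubles the variance of the treatment contrast under the protocol's own model; using the baselines as a covariate would cut the interval half-width from about 1.4 to 1.1 rmse

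*Protocol*

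**What the plan says.** Section 26 of the protocol (Power Analysis) describes a "two-period crossover study design with baseline and follow-up measurements for each period". Under Stool Collection, the samples after the pre-treatment one are taken "after completing the first study arm at week 5, after completing the washout period at week 7, and after completing the second arm" at week 12. Week 0 and week 7 are thus the period baselines, and weeks 5 and 12 the end-of-period values.

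The quantity to be estimated is the "mean within-child between-period (synbiotic vs. prebiotic) difference in within-period change (from baseline to follow-up". The error model has a single residual component, (1 − R) × V, "where R is the within-child correlation and V is the total variance of the outcome distribution"; the rmse is its square root. "With an analysis of ten children", the margins of error ("i.e. halfwidths of 95% confidence intervals) will be 1.4 root mean square error (rmse) wide") are derived from this, together with 80% power "to detect differences of magnitude 1.94 rmse" at a two-sided 5% level. Section 26 then converts these to SD units at R = 0.4 and R = 0.7. It says that no estimate of R exists for this population and that 40% comes from infants. It mentions no covariate adjustment and gives no reason, such as carry-over, for subtracting the baselines.

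**The concern.** In a crossover, the comparison of a child with itself already removes the stable difference between children. Subtracting a baseline helps only if it tracks something specific to its own period. A model with one common within-child correlation has no such component, so each baseline enters the contrast as one more noisy measurement.

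This matters because the trial hopes for ten completers and section 26 rests its value on precise estimates. At R = 0.4 the stated detectable difference is 1.5 SD, which only a very large effect would reach. Precision is the scarce resource, and the same four samples can give more of it.

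**Working it through.** **Inputs.** From section 26: n = 10, two-sided 5%, residual variance (1 − R)V = rmse², R = 0.4 or 0.7. From Stool Collection: samples at weeks 0, 5, 7 and 12. Write Y for an end-of-period value and B for a period baseline. For each child, d_Y = Y(synbiotic) − Y(BMO) and d_B = B(synbiotic) − B(BMO).

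**1. Variances under the protocol's model.**
- Var(d_Y) = 2(1 − R)V = 2 rmse².
- Var(d_B) = 2 rmse².
- Cov(d_Y, d_B) = (R − R − R + R)V = 0.
- Var(d_Y − d_B) = 2 + 2 = 4 rmse², exactly double at any R.

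**2. Reproducing the stated figures.** With variance 4, the standard error is √(4/10) = 0.632 rmse. The protocol does not state degrees of freedom (df); 10 df reproduces both figures:
- margin: 2.228 × 0.632 = 1.41 rmse (stated 1.4);
- detectable difference: (2.228 + 0.842) × 0.632 = 1.94 rmse (stated 1.94).

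A paired t with 9 df gives 1.43 and 1.96. With variance 2 the same formulas at 10 df give 1.00 and 1.37 rmse, which do not match. The stated figures therefore belong to the unadjusted difference of change scores. Multiplying by √(1 − R) gives 1.1 and 1.5 SD at R = 0.4, as stated. At R = 0.7 it gives 0.77 and 1.06 SD; the first does not fit the protocol's claim of less than 0.7 SD, which is a separate slip.

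**3. Effect of adjusting instead of subtracting.** Regress d_Y on an intercept (treatment), a sequence indicator (period) and d_B. Estimating the slope inflates the variance by 1 + 1/(10 − 4) = 1.167, so the variance ratio at n = 10 is 2/1.167 = 1.71 rather than 2. Simulation (30,000 trials, 5:5 split, period term in both analyses):

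| Estimator | Mean 95% half-width | Power at 1.94 rmse |
|---|---|---|
| Change-score contrast | 1.41 rmse | 77% |
| Adjusted for d_B | 1.09 rmse | 93% |

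The adjusted analysis reaches 80% power at about 1.58 rmse. In SD units, its half-width is 1.09 × √0.6 = 0.85 SD at R = 0.4 and 1.09 × √0.3 = 0.60 SD at R = 0.7.

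**4. Outside the single-correlation model (assumed values).** Let w be the correlation between baseline and follow-up in the same period, and b the correlation across periods. Then Var(d_Y − d_B) = 4(1 − w)V. The slope is (w − b)/(1 − b), and the large-sample variance ratio is 2/(1 + slope).

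| w, b | Slope | Large-sample ratio |
|---|---|---|
| 0.4, 0.4 | 0 | 2.0 |
| 0.6, 0.4 | 0.33 | 1.5 |
| 0.8, 0.4 | 0.67 | 1.2 |
| 0.9, 0.7 | 0.67 | 1.2 |
| 0.95, 0.7 | 0.83 | 1.09 |

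At n = 10 the cost of estimating the slope uses up a ratio of 1.2. Simulated half-widths tie at 0.8/0.4 (0.633 against 0.631 SD) and at 0.9/0.7 (0.444 against 0.443 SD). At 0.95/0.7 subtraction would be slightly ahead: 0.200V against 0.183V × 1.167 = 0.214V.

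**5. Carry-over.** Assume a true effect of 1.0 SD and a synbiotic residual of 0.5 SD, which affects only the half of the children who took the synbiotic first, so it moves the mean by 0.5 × 0.5 = 0.25 SD.
- Residual present at week 7, gone by week 12: subtraction gives 1.0 + 0.25 = 1.25; the adjusted estimate stays at 1.0.
- Residual equal at weeks 7 and 12: subtraction gives 1.0; the adjusted estimate, with slope near 0, gives 1.0 − 0.25 = 0.75.

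**6. Linear time trend.** At an assumed 0.1 SD per week, each 5-week change gains 0.5 SD and the two cancel, whatever the split between sequences. A raw comparison of weeks 5 and 12 does not cancel it: 7 weeks × 0.1 = 0.7 SD, and a 6:4 split passes on (6 − 4)/10 × 0.7 = 0.14 SD. This is why the adjusted analysis needs its period term.

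**The case against.** The strongest reply is that the planned contrast is valid and conventional, that its precision is openly stated, and that change is the declared endpoint (section 10). The cited text also defines a parameter in a power paragraph and does not rule out a covariate; an analysis plan that is not shown may include one. Much of this stands. The parameter need not be redefined: without carry-over both estimators target the same treatment effect, and regressing d_Y − d_B on d_B gives the same treatment coefficient as regressing d_Y on d_B. What remains is that the only method and precision figures stated are those of the unadjusted contrast.

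The gain also depends on a correlation structure that nobody has measured in these children. That stands as well, and step 4 shows where it disappears.

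Three stronger readings are tempting and are not supported:
- **That any time trend leaks into the planned contrast when sequences are unequal.** A linear trend cancels because both periods last five weeks; only a trend that differs between the periods would leak.
- **That carry-over can only flatter the synbiotic under subtraction.** It does so if the residual fades by week 12. If it persists equally, the adjusted estimate is the biased one. With a live organism and a two-week washout, neither pattern can be excluded from the document.
- **That the change costs nothing.** It needs no new samples, but the slope takes a degree of freedom and about 17% in variance at n = 10.

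**Conclusion.** The point holds as one of precision. Under the protocol's own model the change-score contrast has exactly twice the variance of the end-of-period contrast, and the figures 1.4 and 1.94 rmse contain that doubling. After paying for the estimated slope and a period term, adjustment narrows the interval by about 22% (1.41 to 1.09 rmse) and raises power at 1.94 rmse from about 77% to 93%.

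This rests on ten completers split 5:5, one common within-child correlation and no carry-over. The gain is smaller if measurements in the same period are more alike than measurements across periods. It is nil at n = 10 once the baseline slope reaches about two thirds. The planned analysis is not invalid, and a reader should not infer bias from this point: which estimator is biased under carry-over depends on how long the residual lasts.

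**What to change.** In section 26, keep the synbiotic-versus-BMO treatment effect as the target. State that it will be estimated from the week-5 and week-12 values with treatment and period terms, and with the within-child difference in period baselines (week 0, week 7) as a covariate. Restate the margin of error and detectable difference for that analysis: about 1.1 and 1.6 rmse under the present model, with the range in step 4 as a caveat. Recheck the SD figures at R = 0.7 at the same time. Report the change-score contrast as a sensitivity analysis and say in advance that a gap between the two estimates may reflect carry-over, with the direction explained as in step 5.

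The cost is wording, one degree of freedom for the slope and one for the period term. All four samples per child are already planned, and no study procedure changes.

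### Protocol section 26: the margin of error given for a within-child correlation of 0.7 (below 0.7 SD) does not follow from the protocol's own formula, which gives 0.77 SD

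*Protocol*

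**What the plan says.** The Power Analysis in Protocol section 26 is based on ten analysed children in a "two-period crossover study design with baseline and follow-up measurements for each period". The parameter is the "mean within-child between-period (synbiotic vs. prebiotic) difference in within-period change (from baseline to follow-up").

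Two results are given in units of the root mean square error (rmse). The "margins of error (i.e. halfwidths of 95% confidence intervals) will be 1.4 root mean square error (rmse) wide", and there is 80% power "to detect differences of magnitude 1.94 rmse, under two-sided testing" at the 5% level.

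The section defines the residual variance as (1 − R)V and the rmse as its square root. It uses these expressions to convert both results to units of the total standard deviation, SD = √V:

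- At R = 0.4, called the conservative assumption, the margin of error is 1.1 SD and the detectable difference 1.5 SD.
- At R = 0.7, the optimistic case, "the margin of error and the minimum detectable difference will be less than 0.7 and 1.1 SD, respectively".

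It concludes that precision is sufficient for the pilot's objectives over the whole range from 0.4 to 0.7.

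**The concern.** The conversion from rmse to SD is a single multiplication by √(1 − R), so all four SD figures can be checked directly. Three of them come out as printed. The margin of error at R = 0.7 does not, and the discrepancy is in the favourable direction.

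The sample size is justified mainly by precision, and this figure is the favourable end of the precision range. The section also says that the pilot should inform later research in this population, so a bound that is too small could be carried into another study's planning.

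**Working it through.** **Inputs, all from Protocol section 26:** margin of error 1.4 rmse; detectable difference 1.94 rmse; rmse = √((1 − R)V); R = 0.4 and R = 0.7; ten children.

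**Formula:** figure in SD = figure in rmse × √(1 − R).

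**Step 1. Conversion factors.** At R = 0.4, √0.6 = 0.775. At R = 0.7, √0.3 = 0.548.

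**Step 2. The four SD figures.**

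| R | Quantity | Calculation | Result | Protocol states | Agrees? |
|---|---|---|---|---|---|
| 0.4 | Margin of error | 1.4 × 0.775 | 1.08 SD | 1.1 SD | yes |
| 0.4 | Detectable difference | 1.94 × 0.775 | 1.50 SD | 1.5 SD | yes |
| 0.7 | Detectable difference | 1.94 × 0.548 | 1.06 SD | below 1.1 SD | yes |
| 0.7 | Margin of error | 1.4 × 0.548 | 0.767 SD | below 0.7 SD | **no** |

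**Step 3. Could rounding of the 1.4 explain it?** Values that round to 1.4 run from 1.35 to 1.45. They give 1.35 × 0.548 = 0.74 SD to 1.45 × 0.548 = 0.79 SD. None is below 0.7.

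**Step 4. What would make the bound true?**

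- A higher correlation: 1.4 × √(1 − R) < 0.7 requires 1 − R < (0.7/1.4)² = 0.25, so R > 0.75. The section considers 0.4 to 0.7.
- A smaller margin: 0.7/0.548 = 1.28, so the margin would have to be below 1.28 rmse, which does not round to 1.4.

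**Step 5. Could another quantile explain it?** If residuals are independent, a difference of two changes has variance 4 rmse² per child, so the standard error is 2/√10 = 0.632 rmse. A normal quantile then gives 1.96 × 0.632 = 1.24 rmse, which is 0.68 SD at R = 0.7. This meets the bound but contradicts the stated 1.4 rmse, and at R = 0.4 it gives 1.24 × 0.775 = 0.96 SD, not the stated 1.1 SD. With a t quantile, the bound needs a value below 1.278/0.632 = 2.021, which takes more than 40 degrees of freedom. Ten children with four measurements each supply only 40 observations.

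**Step 6. Size.** (0.767 − 0.7)/0.767 = 0.087, so the stated bound is about 9% below the protocol's own result.

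**The case against.** The strongest reply is that nothing depends on this number. The planning case is R = 0.4, and its figures are right. R = 0.7 is offered only as an optimistic case. The target of ten completers does not depend on it, and no endpoint or analysis changes. The protocol sets no precision threshold and accepts 1.1 SD at R = 0.4 as sufficient, so 0.77 SD in place of 0.7 SD at R = 0.7 cannot overturn its conclusion. All of this stands. It limits the importance of the error but does not remove it.

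A reader might also infer that the 80% power claim is wrong, because an exact paired t-test on ten differences (9 degrees of freedom) has 77.9% power at 1.94 rmse. The document does not support that inference. It fixes neither the degrees of freedom nor the method of calculating power, and these may properly be left to the statistical analysis plan. Exact power at 1.94 rmse runs from 76.6% on 8 degrees of freedom to 80.4% on 12. The usual approximation that adds a t quantile and a normal quantile returns, on 10 degrees of freedom, (2.228 + 0.842) × 0.632 = 1.94 rmse, the printed figure. Nor is the 1.4 rmse in doubt: every value from 9 degrees of freedom (1.431) to 14 (1.356) rounds to it. Neither rmse figure is shown to be wrong.

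**Conclusion.** One figure is wrong as written. The margin of error at a within-child correlation of 0.7 is 0.77 SD (0.74 to 0.79 SD allowing for rounding of the 1.4), not below 0.7 SD. This rests only on the protocol's stated 1.4 rmse and its definition of the rmse; it needs no assumption about degrees of freedom or the analysis model.

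The severity is minor. The error flatters the best case, but the sample size, the R = 0.4 planning case and the general statement about sufficient precision are unaffected.

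**What to change.** In the R = 0.7 sentence of Protocol section 26, change the bound on the margin of error from 0.7 SD to 0.8 SD, or state it as about 0.77 SD. Leave the bound of 1.1 SD on the detectable difference, the two rmse figures and the R = 0.4 figures as they are.

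The cost is one corrected number. No change to the design, sample size or analysis follows from it.
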